# Gabapentin to achieve HIV viral load suppression in people with risky drinking in Mbarara, Uganda: study protocol for a randomized, double-blinded, placebo-controlled trial (GRAIL)

**DOI:** 10.21203/rs.3.rs-6856284/v1

**Published:** 2025-10-15

**Keywords:** Uganda, HIV, Alcohol Use, Viral Load Suppression, Gabapentin, RCT

## Abstract

**Background::**

Ending the HIV epidemic requires achieving HIV viral load (HVL) suppression for key populations including those with risky drinking. Gabapentin can decrease alcohol use and thus holds potential for improving medication adherence and HIV viral load suppression for individuals with HIV and risky drinking.

**Methods::**

To describe the protocol for arandomized, double-blinded, placebo-controlled trial, (GRAIL [Gabapentin to Reduce Alcohol and Improve viral Load suppression]), to test the efficacy of gabapentin versus placebo on achieving undetectable HIV viral load among people with HIV with risky drinking. We recruit and randomize 300 people with detectable HIV viral loads (>= 200 copies/ml) and risky drinking. Participants are randomized 1:1 to receive either gabapentin (1800 mg/day target dose) or placebo for 3 months in a double blind design. Both arms receive a 5-minute evidence-based counseling session aimed at reducing alcohol use. The primary outcome is undetectable viral load (<200 copies/ml) at 3 months. Other secondary outcomes include undetectable viral load at 6 and 12 months, biomarker-confirmed recent alcohol consumption, antiretroviral therapy (ART) adherence, engagement in HIV care and pain severity. This study takes place in Mbarara, Uganda, as the country ranks among the top five for alcohol consumption globally and has 1.4 million people living with HIV.

**Discussion::**

GRAIL tests the efficacy of gabapentin, a medication to decrease alcohol use to achieve HIV viral load suppression. This trial may identify a treatment strategy to prevent the transmission of HIV and improve health outcomes among a high risk HIV population, specifically those with risky drinking.

**Trial registration::**

This trial has been registered at ClinicalTrials.gov (NCT05443555) on June 29, 2022. https://clinicaltrials.gov/study/NCT05443555?term=NCT05443555&rank=1

## Background

Over 1.4 million people in Uganda are living with HIV. Among this group, 90% are aware of their HIV status, 84% report receiving antiretroviral therapy (ART), and 79% of people with HIV (PWH) have achieved HIV viral load (HVL) suppression [1]. These statistics represent great progress, yet the country is facing barriers on its path to achieving the UNAIDS 95–95-95 HIV targets (i.e., detection, on medication, HVL suppression) [2]. The prevalence of heavy drinking is high in Uganda; its per capita alcohol consumption of 12 liters of alcohol per year places Uganda at the top of the list among African countries for alcohol consumption[3] and in the top five globally [4]. Alcohol consumption has negative impacts across the HIV care cascade, including effects on engagement in HIV care (i.e., individuals who are “Linked and Retained”), medication adherence, and HVL suppression [5, 6]. An intervention targeting alcohol consumption in PWH with heavy alcohol use and without HVL suppression has the potential to improve HIV outcomes such as medication adherence and HVL suppression. Increasing viral suppression rates could decrease the incidence of new HIV infections exemplifying “treatment as prevention”. Gabapentin has been shown to be an effective treatment for alcohol use disorder [7–10] and neuropathic pain [11], but its impact on outcomes in PWH with heavy alcohol use has not been evaluated [7–10]. Uganda’s high HIV and alcohol use burden make this setting suitable for studying gabapentin in this population.

This paper describes the protocol of the Gabapentin to Reduce Alcohol and Improve viral Load suppression (GRAIL) – Promoting “Treatment as Prevention”, randomized, double-blinded, placebo-controlled clinical trial among 300 people with unsuppressed HIV and risky drinking to evaluate the efficacy of gabapentin in promoting HVL suppression.

## Methods

GRAIL is a randomized, double-blinded, placebo-controlled clinical trial designed to evaluate the efficacy of gabapentin versus placebo in achieving undetectable HVL in 300 PWH who engage in recent risky drinking. Risky drinking is operationalized as a positive Alcohol Use Disorders Identification Test - Concise (AUDIT-C) and urine ethyl glucuronide (EtG) test. Participants are randomized 1:1 to receive either gabapentin or placebo for 3 months; both arms receive a brief intervention to reduce alcohol use.

### Study setting

The study is being implemented at Mbarara University of Science and Technology (MUST) in Mbarara, Uganda. MUST is a major educational, scientific, and clinical medical institution. Recruitment occurs at the Immune Suppression Syndrome (ISS) Clinic at the Mbarara Regional Referral Hospital in Uganda, HIV Care Clinics (e.g., Mbarara City Council Health Centre 4 and others within and outside the city and district), as well as through snowball recruitment. The ISS Clinic has provided HIV care since November 1998. The adult care section of the clinic currently cares for over 11,500 adults with HIV. The SPIRIT checklist of recommended items to address in a clinical trial protocol is available as Additional File 1. See Fig. 1 for study flow and Fig. 2 for the planned schedule of enrollment, intervention and assessments.

### Participants and recruitment

In Uganda, clinics typically initiate ART for patients newly diagnosed with HIV. Therefore, our criteria require that a participant has been diagnosed with HIV for at least six months, and their detectable HVL must be recorded at least six months post-diagnosis to strongly suggest non-adherence to ART. Participants are eligible if they meet the following additional criteria: 18 years or older; positive EtG urine test (300 ng/ml cutoff); able and willing to comply with all protocols and procedures; and living within 2 hours travel time of the study site. They are excluded for the following: not fluent in English or Runyankole; cognitive impairment resulting in inability to provide informed consent based on research assistant assessment; pregnant, planning to become pregnant in the next 3 months, or breastfeeding; taking gabapentin/pregabalin in past 30 days; taking any medication for alcohol use disorder; known hypersensitivity to gabapentin; enrolled in another HIV research study seeking viral load suppression; and has an unstable psychiatric illness. Study eligibility criteria are detailed in Table 1. A clinic staff member reviews electronic medical records to identify patients with upcoming clinic appointments who potentially meet eligibility criteria. Patients meeting the initial eligibility criteria (i.e., HIV diagnosis and most recent detectable HVL) are approached during their appointment to assess interest in study participation. Those interested are screened by a study research assistant (RA), who is a clinical officer, to determine further eligibility. In addition, the GRAIL study data manager and project coordinator consult with clinic counselors overseeing the non-suppression registry to identify patients with a recent detectable HVL test who were not captured through the initial screening process.

RAs either meets potential participants at the clinics following their routine clinic visit or makes an appointment to meet in person at a later date at one of the recruitment clinics. For participants unable to travel to the clinic, RAs provides transportation from their home to the clinic. RAs introduce the study to eligible participants, gauge their interest and explain the purpose of the study. If further eligibility is established, the RA seeks informed consent. Randomization follows the completion of the baseline assessment.

### Randomization

Randomization is conducted and monitored by the data management team. Participants are randomized in a 1:1 ratio using permuted blocks with a fixed block size of two, stratified by: i) self-reported alcohol use severity score (Alcohol Use Disorders Test (AUDIT) > 20 vs. ≤ 20) and ii) clinic site. We assumed participants with severe alcohol use may be less likely to reach HVL suppression over the study period than those who are drinking less alcohol.

Randomized group allocations are concealed using scratch-off cards. Before recruitment, the study pharmacist received a randomization list containing sequential card numbers for ordering and a unique 5-digit code (randomization result) indicating the medication assigned arm (gabapentin and placebo). Each scratch-off card displays only the card number, while the randomization code remains hidden until the participant scratches off the covering. The AUDIT score stratum is distinguished by the color of the scratch card (i.e., yellow for AUDIT > 20 and green for AUDIT ≤ 20).

During randomization, RAs present participants with the top four sequential scratch-off cards from the appropriate AUDIT pile. Participants select one card, scratch it off, and reveal the randomization result. Based on the result, the RA provides the corresponding medication package labeled with that unique randomization number. The next sequential card is then added to the pile, ensuring that four cards are consistently available for subsequent participants.

### Intervention

Eligible participants are then randomly assigned into one of two study arms: 1) gabapentin (up to 600mg [2 pills] three times a day, i.e., 1800mg/day target dose) for 3 months vs. 2) placebo for 3 months. At baseline, all participants will receive brief (5 minutes) evidence-based counseling based on the severity of their alcohol use disorder (per DSM-5) from the study assessment. This counseling approach was adapted from the NIAAA Clinician’s Guide [12]. Participants who continue to meet the criteria for alcohol use disorder at 3 months are offered additional alcohol counseling sessions with GRAIL study counselors. At study initiation, the medication is provided by trained clinical officers, who instruct participants in proper medication administration and adherence.

Study medications were purchased from the Gama Pharmaceuticals (U) Ltd and EVA Pharma. Placebo medications do not contain active ingredients. The placebo and active study medications are indistinguishable by packaging, appearance and taste to allow for double blinding. The study pharmacist packages study medications into paper envelopes. Participants and study team members are blinded to assigned treatment.

Medication dosing is based on Mason et al [8]. Dosing is titrated up over 3 weeks, starting with a daily dose of 300mg (1 capsule/day) in week 1, followed by a daily dose of 900mg (3 capsules/day) in week 2, up to a target daily dose of 1800mg (6 capsules/day) in week 3. The target dose of 1800mg per day is sustained from weeks 3 through day 4 of week 12. Then, the dose is tapered down to 900mg in days 5–7 of week 12, and medication is discontinued at the end of week 12. If a participant in any group experiences an adverse event, the symptom is documented and monitored at each study visit. If reductions in medication are required due to side effects, the participant will be advised to reduce their dose to that of the prior week. The GRAIL medication schedule can be seen in Table 2. Participants are instructed to bring any unused capsules to their upcoming in-person study visit.

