### Study outcomes

The primary outcome is undetectable HVL (< 200 copies/ml) at 3 months, with secondary outcomes being undetectable HVL at 6 and 12 months. In order to explore potential mechanisms by which gabapentin may lead to HVL suppression, we assess the impact of gabapentin compared to placebo on the following secondary outcomes: a) alcohol consumption; b) pain severity; c) ART adherence; and d) engagement in HIV care.

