### Questionnaires

Participants are assessed at baseline, 3, 6, and 12 months post enrollment, along with shorter medication visits by phone at weeks 1, 3, 6 and 10 and shorter medication visits in-person at weeks 2, 4 and 8. All follow-up study visits take place at the clinic from where the participant was recruited or by phone.

Participants receive a meal at each study visit, along with either 1 kg of rice and one bar of soap, or two bars of soap, as compensation. Transport costs are also reimbursed: 20,000 UGX (5.33 USD) for those living within 20 km, 30,000 UGX (8 USD) for 20–40km, and up to 45,000 UGX (12 USD) for 40–60km from the study site.

The study has employed a driver to provide transportation to the clinic for participants who require a ride to their study visit appointments.

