### Analytic methods

The study uses an intention-to-treat analysis that includes all participants according to their randomized assignment. Descriptive statistics are calculated for variables at baseline and each follow-up time to assess whether there appear to be any differences across treatment arms. Spearman correlation analyses are performed to identify pairs of variables that may be collinear. In addition, the variance inflation factor is assessed to detect possible collinearity.

The primary outcome for this study is undetectable HVL (< 200 copies/ml) at 3 months. The primary analysis uses multivariable logistic regression analyses to control for the randomization stratification factors to improve efficiency (i.e., AUDIT > 20, clinic site). If any baseline factors appear to differ by randomized group, additional sensitivity analyses will be conducted controlling for these factors to assess for potential confounding. Other binary outcomes (e.g., heavy alcohol consumption [defined as PEth ≥ 50 ng/mL], adherence to ART [defined as taking ≥ 80% of prescribed medication via Visual Analog Scale], engagement in HIV care [defined as ≥ 1 HIV visit in the past 3 months]) will be analyzed using the same approach. Number of heavy drinking days (assessed using the Timeline Followback [TLFB] method) in the past month will be analyzed using negative binominal regression, to account for overdispersion in the data. Percentage of ART pills taken (assessed by self-report), a continuous outcome, will be analyzed using multiple linear regression if the data are normally distributed. However, if the distribution is skewed, transformations of the data will be performed (e.g., log transformation). If an appropriate transformation is not identified, a median regression model will be used. A secondary analysis will be conducted using a per protocol approach that includes only those participants who were adherent to their assigned intervention (i.e., defined as taking at least 80% of the assigned medication), as determined by self-report (i.e., Visual Analog Scale).

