**Exclusion Criteria**
Not fluent in English or Runyankole
Cognitive impairment resulting in inability to provide informed consent based on research assistant assessment
Pregnancy, planning to become pregnant in next 3 months, or breast feeding (pregnancy assessed via study test)
Taking gabapentin/pregabalin in past 30 days (self-report)
Taking any medication for alcohol use disorder (self-report)
Known hypersensitivity to gabapentin (self-report)
Enrolled in another HIV research study seeking viral load suppression (self-report)
Unstable psychiatric illness (i.e., answered yes to any of the following: past three month active hallucinations; mental health symptoms prompting a visit to the ED or hospital; mental health medication changes due to worsening symptoms; presence of suicidal ideations)

**Table 2 T2:** GRAIL medication dosing schedule

Week 1: 1 capsule per day; 7 capsules total							
	Day 1	Day 2	Day 3	Day 4	Day 5	Day 6	Day 7
Morning	1 capsule	1 capsule	1 capsule	1 capsule	1 capsule	1 capsule	1 capsule
Afternoon							
Evening							
Total	1	1	1	1	1	1	1
Week 2: 3 capsule per day; 21 capsules total							
	Day 1	Day 2	Day 3	Day 4	Day 5	Day 6	Day 7
Morning	1 capsule	1 capsule	1 capsule	1 capsule	1 capsule	1 capsule	1 capsule
Afternoon	1 capsule	1 capsule	1 capsule	1 capsule	1 capsule	1 capsule	1 capsule
Evening	1 capsule	1 capsule	1 capsule	1 capsule	1 capsule	1 capsule	1 capsule
Total	3	3	3	3	3	3	3
Week 3, 4, 5, 6, 7, 8, 9, 10, 11: 6 capsule per day; 42 capsules total							
	Day 1	Day 2	Day 3	Day 4	Day 5	Day 6	Day 7
Morning	2 capsules	2 capsules	2 capsules	2 capsules	2 capsules	2 capsules	2 capsules
Afternoon	2 capsules	2 capsules	2 capsules	2 capsules	2 capsules	2 capsules	2 capsules
Evening	2 capsules	2 capsules	2 capsules	2 capsules	2 capsules	2 capsules	2 capsules
Total	6	6	6	6	6	6	6
Week 12: 33 capsules total							
	Day 1	Day 2	Day 3	Day 4	Day 5	Day 6	Day 7
Morning	2 capsules	2 capsules	2 capsules	2 capsules	1 capsule	1 capsule	1 capsule
Afternoon	2 capsules	2 capsules	2 capsules	2 capsules	1 capsule	1 capsule	1 capsule
Evening	2 capsules	2 capsules	2 capsules	2 capsules	1 capsule	1 capsule	1 capsule
Total	6	6	6	6	3	3	3

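### If the 3-month visit falls at calendar 3 months, the past-month count of heavy drinking days is partly off drug, which weakens its use as evidence of an on-drug mechanism

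*Protocol article*

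**What the plan says.** The abstract describes participants as receiving "either gabapentin (1800 mg/day target dose) or placebo for 3 months in a double blind design", and the opening of Methods repeats the duration: "Participants are randomized 1:1 to receive either gabapentin or placebo for 3 months". The Intervention section gives the calendar. Participants reach 1800 mg daily in week 3 and stay on it until the fourth day of the final week. For the end of the course the section states: "the dose is tapered down to 900mg in days 5–7 of week 12, and medication is discontinued at the end of week 12". Table 2 agrees ("Week 12: 33 capsules total").

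Outcome visits are set in months: "Participants are assessed at baseline, 3, 6, and 12 months post enrollment" (Questionnaires). The same sentence sets the shorter medication contacts in weeks; the last two are week 8 (in person) and week 10 (by phone). Neither a study day nor a window is given for the 3-month visit.

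Study outcomes lists alcohol consumption, pain severity, ART adherence and engagement in care as secondary outcomes, chosen "In order to explore potential mechanisms by which gabapentin may lead to HVL suppression". Analytic methods defines one of the drinking measures as "Number of heavy drinking days (assessed using the Timeline Followback [TLFB] method) in the past month", to be analysed by negative binomial regression. The other is PEth (phosphatidylethanol), tested at baseline and 3 months.

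**The concern.** A mechanism outcome should be measured while the supposed mechanism is operating. Here treatment is called 3 months long and the outcome is taken at 3 months, so a reader will assume that the outcome reflects time on target dose. The dosing calendar says otherwise: the dose has been halved from day 82, and at a visit one calendar quarter after enrolment dosing has been over for about a week.

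A count over the preceding month then adds days on target dose, days on half dose and days on nothing. Days without drug add noise but little or no drug effect, so the arms are pulled together. A real reduction in heavy drinking during treatment could be missed and reported as no effect on drinking. That would distort the account of how gabapentin did or did not change viral suppression. The primary viral load outcome is not at issue.

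**Working it through.** **Step 1: dosing calendar (Intervention, Table 2).** Weeks 1–11 are days 1–77, so week 12 day 4 is day 77 + 4 = 81 and the last dose is on day 84. Week 12 capsules: 4 × 6 + 3 × 3 = 33, which reproduces the Table 2 total. Target-dose days: weeks 3–11 plus four days = 9 × 7 + 4 = 67 (days 15–81).

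**Step 2: visit day (assumed).** The article does not give it. Range used: day 84–85 if 3 months means 12 weeks, and day 91–92 if it means calendar months.

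**Step 3: contents of a 30-day recall window.** Each visit is counted two ways: window ending the day before the visit (A), or on the visit day (B).

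| Visit day | Count | Target | Half | Off | Below target | Off drug |
|---|---|---|---|---|---|---|
| 84 | A | 28 | 2 | 0 | 7% | 0% |
| 84 | B | 27 | 3 | 0 | 10% | 0% |
| 85 | A | 27 | 3 | 0 | 10% | 0% |
| 85 | B | 26 | 3 | 1 | 13% | 3% |
| 91 | A | 21 | 3 | 6 | 30% | 20% |
| 91 | B | 20 | 3 | 7 | 33% | 23% |
| 92 | A | 20 | 3 | 7 | 33% | 23% |
| 92 | B | 19 | 3 | 8 | 37% | 27% |

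**Step 4: dilution.** Assume that the effect ends with dosing, and that a half-dose day carries between half and all of the effect. The share of the on-drug contrast that remains lies between (target + half/2)/30 and (target + half)/30.

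- Day 91–92, lowest: (19 + 1.5)/30 = 0.68. Highest: (21 + 3)/30 = 0.80.
- Day 84–85: 0.95 to 1.00, or 0.92 to 0.97 in the single case (85, B) where an off-drug visit day is itself counted.

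**Step 5: what this means for power (illustration).** The article states no power for this outcome. Take as an assumption a test that would have 80% power if every recalled day were on target dose; its expected z is 1.96 + 0.84 = 2.80. With variance unchanged, power = Φ(2.80 × share − 1.96).

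- Day 91: share 0.717 to 0.80 gives Φ(0.05) = 52% to Φ(0.28) = 61%.
- Day 92: share 0.683 to 0.767 gives 48% to 57%.
- Day 84: share 0.95 to 1.00 gives Φ(0.70) = 76% to 80%.

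**Step 6: does dropping the later days help?** With only the t target-dose days in the window, the full effect is kept but there are fewer days per person. Let r be the part of the 30-day variance that is pure counting noise, the rest being stable differences between people (overdispersion). The variance is multiplied by 1 + r(30/t − 1), so power = Φ(2.80/√[1 + r(30/t − 1)] − 1.96). The value of r is not in the article; I take 0.05 to 0.30 as an overdispersed range.

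- Day 91, t = 20: r = 0.30 gives 2.80/√1.15 = 2.61, power 74%; r = 0.05 gives 2.80/√1.025 = 2.77, power 79%.
- Extreme case with no overdispersion, r = 1: 2.80/√1.5 = 2.29, power 63%, against 52–57% for the full window on the same count.

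If the effect ends with dosing, the restricted analysis is better throughout. If the effect persists past day 84, the full window has 80% and the restricted one 74–79%.

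**The case against.** The strongest reply is that the visit day is unknown. The article uses 3 months for a 12-week course and the same words for the visit, and symptom checks every two weeks after the first month would put the next contact after week 10 at week 12. On that reading the visit is at about day 84–85 and almost nothing is lost. This stands, and it is why the size is given as conditional. The counter-indication is that the Questionnaires section sets medication contacts in weeks and outcome visits in months within one sentence, which makes a calendar reading natural. Visit windows are also a detail that an article may leave to the full protocol, so their absence is not itself a fault.

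Three stronger readings are tempting, and the article does not support them.

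- **Drug always stopped before the outcome visit.** This is not established, because a day-84 visit falls on the last day of the taper.
- **Pain wholly off drug.** The instrument appears only in the abbreviation list, without a recall period. With an assumed 7-day recall ending the day before the visit, the off-drug share is 0% at day 85, 86% at day 91 and 100% at day 92. Pain may be affected, but the extent cannot be fixed.
- **All drinking outcomes diluted.** No detection window is given for PEth, so no dilution of it is shown.

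Nor can one say that nothing is measured on treatment. The assessment components are in Table 3 and the schedule is in Figure 2, neither of which was readable in the text available to me.

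It is also fair that these outcomes are secondary and exploratory, that measuring them at the primary visit is coherent, and that the 6- and 12-month visits are intended as post-treatment follow-up. The power figures in the working are illustrative, since the 80% starting point is assumed.

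**Conclusion.** The concern holds in conditional form and is limited to heavy drinking days. Target dosing ends on day 81 and all dosing on day 84, so a past-month count at day 91–92 contains 9–11 days below target dose, of which 6–8 are off drug. The on-drug contrast is then about 68–80% of its size, assuming that the effect ends with dosing. About two thirds of the window is still at target dose, so the dilution is moderate. At day 84–85 it is negligible.

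The 3-month intention-to-treat result remains a valid comparison of the two assigned strategies. What it cannot safely carry, if the visit is at calendar 3 months, is the conclusion that gabapentin does or does not reduce heavy drinking while it is being taken. This is an inexpensive improvement to a secondary analysis and does not threaten the primary result.

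**What to change.** Leave the dosing schedule, the visit schedule and the past-month outcome as they are. Before unblinding, add to the analysis plan an on-treatment analysis of heavy drinking days:

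- use only Timeline Followback days up to and including each participant's planned week 12 day 4;
- fit the planned negative binomial regression with the same stratification covariates and log(number of recalled days used) as an offset;
- report it beside the full past-month count, and base the mechanism conclusion for drinking on it.

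The cut-off must be the planned date, not the date on which a participant actually stopped. A date fixed by the schedule is unaffected by treatment or adherence, so the randomised comparison is preserved; an actual stop date would not guarantee that.

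The cost is a paragraph of analysis-plan wording, provided that Timeline Followback is stored by day. No new data are collected. The downside is fewer recalled days per person (about 19–21 of 30 at a day 91–92 visit), hence slightly lower precision if the drug effect outlasts dosing.

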### Laboratory testing and results

Blood is collected throughout the study. CD4 count and creatinine are tested at baseline. Phosphatidylethanol (PEth, an alcohol biomarker) [13], is tested at baseline and 3 months. HIV viral loads are tested at 3, 6, and 12 months. Participants with a creatinine clearance of < 60mL/min have their study medication dose reduced per clinical recommendations for prescribing gabapentin for patients with chronic kidney disease. Additionally, at the 3-month study visit, all participants are asked to provide blood for an HIV drug resistance test, however the test is only conducted for those with a detectable HVL at 3 months to assess if the HIV is resistant to that participant’s ART regimen.

Urine samples are collected during screening to test for pregnancy and alcohol use, the latter by using an ethyl glucuronide (EtG) dip test. An EtG dip test is a type of urine test used to detect the presence of alcohol. In this study, we use a test with an 80-hour detection window and a 300 ng/mL cutoff. Additionally, urine is collected for women during in-person medication check-ins and at 3 months to confirm the participant is not pregnant. Participants found to be pregnant will discontinue their study medication but will continue follow-up assessments for the duration of the study.

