### Adverse events and safety monitoring

At baseline, participant symptoms are assessed to document any chronic conditions or symptoms that existed prior to the introduction of study medication. These are documented on the baseline event form and are reviewed and compared to reported adverse events throughout the study. During follow-up, symptoms are assessed weekly for the first month, and biweekly thereafter while the participants are administered study medication. If a participant experiences a severe or medically significant but not immediately life-threatening symptom, the RA increases monitoring frequently for safety, and the team considers adjusting the medication dose or stopping it. Participants may be unblinded if there is an urgent medical need, as determined by the clinician evaluating the participant. If a participant is unblinded, study medication may be discontinued if deemed medically necessary.

Any event that meet the criteria for an adverse event (AE), serious adverse event (SAE), or unanticipated problem is recorded. All events are reviewed by a study physician. AEs and SAEs are periodically presented to and reviewed by an external Data and Safety Monitoring Board (DSMB), the IRBs, and the Uganda’s National Drug Authority.

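### The side-effect rule of going back to the prior week's dose lowers the dose only in weeks 2 and 3; on 60 of the 67 days at 1800 mg it changes nothing

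*Protocol article*

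**What the plan says.** The dosing plan is in the Intervention section and Table 2 of the protocol article. The dose is 300 mg/day in week 1 and 900 mg/day in week 2. After that, "The target dose of 1800mg per day is sustained from weeks 3 through day 4 of week 12." Table 2 agrees: "Week 3, 4, 5, 6, 7, 8, 9, 10, 11: 6 capsule per day; 42 capsules total." For the last three days of week 12, "Then, the dose is tapered down to 900mg" per day, and the drug then stops.

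The paragraph ends with the rule for side effects: "If reductions in medication are required due to side effects, the participant will be advised to reduce their dose to that of the prior week."

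Three other provisions bear on it:

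- The first Questionnaires section sets "shorter medication visits by phone at weeks 1, 3, 6 and 10 and shorter medication visits in-person at weeks 2, 4 and 8," which makes seven check-ins.
- Under Adverse events and safety monitoring, for symptoms that are severe or medically significant but not immediately life-threatening, "the team considers adjusting the medication dose or stopping it." The same section adds: "All events are reviewed by a study physician."
- Under Laboratory testing and results, participants with creatinine clearance below 60 mL/min "have their study medication dose reduced per clinical recommendations" for gabapentin in chronic kidney disease.

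**The concern.** The rule takes effect once a reduction has been judged necessary, so its only job is to say what the lower dose is. It does so by pointing back one calendar week. That equals the previous dose step only while the dose changes weekly, which is in weeks 2 and 3. The sentence comes after the titration, the plateau and the taper have all been described, and nothing in it limits it to titration.

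On the long plateau the prior week's dose is the current dose. Someone handling a non-severe side effect in week 7, say, has an instruction that, taken literally, leaves the participant on 1800 mg. Some staff may read through to the intent and halve the dose, and others may not, so the same complaint could be handled differently. What is at stake is tolerability and consistent conduct, not the trial's inference.

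**Working it through.** **Inputs.** Daily doses come from the Intervention section and Table 2 (300 mg capsules). Check-in weeks come from the first Questionnaires section.

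**Reproducing Table 2.** The weekly capsule totals are 7 × 1 = 7 (week 1), 7 × 3 = 21 (week 2), 7 × 6 = 42 (each of weeks 3 to 11), and 4 × 6 + 3 × 3 = 33 (week 12). All match the table. Days at 1800 mg = 9 × 7 + 4 = 67.

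**Literal rule, day by day.** Compare each day's scheduled dose with the dose seven days earlier.

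| Period | Days | Number of days | Current dose | Prior week's dose | Effect of the rule |
|---|---|---|---|---|---|
| Week 1 | 1–7 | 7 | 300 mg | none | undefined |
| Week 2 | 8–14 | 7 | 900 mg | 300 mg | lower |
| Week 3 | 15–21 | 7 | 1800 mg | 900 mg | lower |
| Week 4 to week 12 day 4 | 22–81 | 60 | 1800 mg | 1800 mg | unchanged |
| Week 12 days 5–7 | 82–84 | 3 | 900 mg | 1800 mg | higher |

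The total is 7 + 7 + 7 + 60 + 3 = 84 days. The rule lowers the dose on 7 + 7 = 14 days. Of the 67 days at 1800 mg, it lowers the dose on 7 and leaves it unchanged on 60, and 60/67 = 89.6%.

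**At the check-ins** (weeks 1, 2, 3, 4, 6, 8 and 10). If the visit falls within its week, the rule gives a lower dose at weeks 2 and 3, the same dose at weeks 4, 6, 8 and 10, and is undefined at week 1. If the visit falls at the end of its week and the rule is applied to the coming week, the dose is lower after weeks 1 and 2 and the same after weeks 3, 4, 6, 8 and 10. Either way, 2 of 7 check-ins yield a lower dose.

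**With a dose-step rule.** Leave out the three taper days, when the drug is already being withdrawn, so 84 − 3 = 81 days remain. All 67 days at 1800 mg step down to 900 mg, and the 7 days of week 2 step down to 300 mg: 67 + 7 = 74, and 74/81 = 91.4%. The literal rule covers 14/81 = 17.3%. The remaining 7 days are week 1, where no lower active step exists.

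These counts describe the standard schedule and do not apply to participants on renally reduced doses.

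**The case against.** The strongest reply is that no sensible reader would apply the rule literally. The sentence tells the participant to reduce, so a reading that leaves the dose alone or raises it contradicts its own verb. It follows a list of doses by week, where the prior week naturally means the prior step. Medication is provided by trained clinical officers, all events go to a physician, and the team may adjust or stop the drug for serious symptoms. Calendar days are also not patients: if intolerance clusters around dose increases (an assumption, since the article gives no timing), the rule works just when it is most needed. Finally, the article condenses a full protocol that may word this better.

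Much of this stands. The previous titration step is the likely intent, a dose increase during the taper is not a realistic outcome, and the day counts say nothing about how many participants are affected. These points keep the matter minor.

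They do not make the rule correct. The separate provision covers only severe or medically significant symptoms and names no dose, so a lesser side effect that still requires a reduction rests on this sentence. Symptoms are assessed weekly in the first month and every two weeks thereafter, so such complaints are looked for throughout the plateau. Nor is this detail left to the full protocol: the article states a rule that, read with its own Table 2, does not deliver the reduction it calls for.

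**Conclusion.** The concern holds, as a minor defect of wording. Read literally on the standard schedule, the rule lowers the dose on 14 of 84 days, all in weeks 2 and 3. It changes nothing on 60 of the 67 days at target dose, and it gives a lower dose at 2 of the 7 medication check-ins. Harm is limited by clinically trained staff, physician review and the separate provision for serious symptoms. The primary intention-to-treat analysis, its error rate and its power are not affected.

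The day counts rest only on the Table 2 schedule. How often the rule would be invoked, and when, cannot be judged from the article.

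**What to change.** Replace the reference to the prior week with *the next lower dose step*: 1800 to 900 mg/day, 900 to 300 mg/day, and at 300 mg/day hold or stop on the clinician's decision. In capsules this is 6 to 3 to 1 per day, so the same instruction serves both arms. Participants already on a renally reduced dose step down from their own adjusted dose as the study clinician decides. Weeks 2 and 3 work exactly as now.

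The essential cost is one phrase in the protocol and a notice to staff; the 300 mg and renal provisions are supporting detail. If the full protocol carries the same phrase, the correction would go through as a new protocol version. Drug supply, capsule strength, blinding and analysis do not change. The Trial status section expects recruitment to run to May 2026, so at publication the correction could still serve participants on study drug.
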